# A study protocol for a pilot randomized controlled trial to evaluate the effectiveness of a gene-based nutrition and lifestyle recommendation for weight management among adults: the MyGeneMyDiet^®^ study

**DOI:** 10.3389/fnut.2023.1238234

**Published:** 2023-08-22

**Keywords:** genotype, lifestyle genomics, nutrigenomics, nutritional genomics, obesity, overweight

## Abstract

**Introduction:**

Managing nutrition and lifestyle practices, nutrition phenotypes, and the genome forms the foundation of precision nutrition. Precision nutrition focuses on metabolic variability among individuals, and one approach to achieving its goals is to integrate gene-based nutrition and lifestyle recommendations in nutrition practice. However, scientific evidence proving the effectiveness of such recommendations is limited. This study will examine whether providing nutrition and lifestyle recommendations based on individual genotype can lead to better weight loss, along with reduction in body mass index (BMI), waist circumference, and body fat percentage among overweight and obese adults.

**Methods and analysis:**

A parallel group, single-blind, randomized controlled trial will be conducted. Sixty-two overweight/obese individuals aged 19–59 years old will be recruited. Participants will be randomly allocated to either the intervention (*n* = 31) or the control arm (*n* = 31). Participants in the intervention group will receive the MyGeneMyDiet^®^ Recommendation for Weight Management, a gene-based nutrition and lifestyle recommendation that was developed based on existing evidence of the effects of *FTO* rs9939609 on body weight, BMI, and physical activity; *UCP1* rs1800592 on calorie intake; and *TCF7L2* rs7903146 on dietary fat intake. Participants in the control group will receive the standard recommendations for weight management. The primary outcomes will be the differences in weight, BMI, waist circumference, and body fat percentage between arms in both the active phase (6 months) and inactive phase (last 6 months) of the trial. Participants in both arms will be evaluated at baseline and in months 3, 6, 9, and 12.

**Discussion:**

To the best of our knowledge, this will be the first gene-based intervention that will adopt a phase of intensive nutrition counseling, followed by a simulation of a free-living state to determine adherence to a gene-based recommendation. This study will contribute to the future implementation of precision nutrition interventions by providing evidence on the effectiveness of a gene-based nutrition and lifestyle recommendation for weight loss.

**Clinical trial registration:**

clinicaltrials.gov, identifier [NCT05098899].

## Introduction

1.

Genetics is one of the factors that influence the variability of responses to weight-loss interventions (1). Certain genetic polymorphisms are believed to affect an individual’s tendency toward obesity and other-related aspects such as appetite control and energy balance (2–4). For instance, the risk allele of *FTO* rs9939609 closely relates to obesity and other related phenotypes in various populations (5–9). Earlier studies have observed the influence of physical activity in this genetic variant, as demonstrated by the significantly higher obesity risk among physically inactive carriers of the risk allele (8–10), and the reduction of such risk among the physically active risk allele carriers (9, 11). On the other hand, mutations in the *UCP1* gene contribute to the development of obesity by reducing energy expenditure modulating the thermogenic function on brown adipose tissue (12, 13). The variant rs1800592 (also known as the -382A/G mutation) is associated with resistance to weight loss in response to energy restriction (14). Carriers of the risk allele for this variant demonstrated lesser weight loss from controlled-energy diet regimen (14, 15), even when exercise is an added regimen to the energy-restricted diet (16). Obese women carrying the ht3 [GAG] haplotype showed accelerated reduction of waist-to-hip ratio and body fat mass when a very low-calorie diet (700 kcal/day) was given to them (17). Moreover, it is becoming apparent that obesity mediates the strong association of *TCF7L2* rs7903146 with type 2 diabetes (18). This variant is associated with obesity risk (19), obesity phenotype (20–22), and several obesity comorbidities such as impaired glucose homeostasis and increased lipid and C-reactive protein levels (23). Dietary intake of saturated fat appears to augment the risk of metabolic syndrome (20) as individuals who carry the risk allele of rs7903146 have better responses to weight loss when fed with a low-fat diet (18). High dietary saturated fat intake accentuates the effect of the variant, implying that dietary fatty acid consumption potentially modifies genetic susceptibility toward metabolic syndrome (20).

Earlier studies have shown that dietary advice based on genetic information resulted in specific changes in the intake of sodium and dietary fat (24, 25). However, substantial research showing the effectiveness of gene-based nutrition recommendations for improving weight and obesity-related outcomes are rather limited. Available evidence showed none or modest improvements in weight, lifestyle, and dietary behavior when advice was linked to genetic profiles (24, 26–28) or when genetic risks were disclosed to the participants (24, 25, 29, 30).

To expand the existing knowledge about the effects of gene-based nutrition and lifestyle recommendations, this randomized controlled trial aims to determine if the provision of the MyGeneMyDiet^®^ Recommendation for Weight Management and disclosure of genetic risk can help overweight/obese individuals achieve 5–10% weight loss in a 12-month trial when compared with the standard advice for weight management. Other primary outcomes include reduction in BMI, waist circumference, and body fat percentage.

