### Sample size calculation

2.5.

To address the primary research question, at least 52 participants (*n* = 26 per group) are needed to detect a clinically meaningful difference of 5% weight loss after 6 months of intervention, assuming 80% power, an alpha of 5%, and a 0.25 SD in the main outcome variable (31). We aim to recruit 62 participants (*n* = 31 per group) to account for the potential dropout rate of 20%.

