### Outcomes

2.7.

The primary outcomes will be the difference in weight, BMI, waist circumference, and body fat percentage between the arms after both the active and inactive phases. Secondary outcomes will include improvement in dietary intake, eating behavior, physical activity levels, glycated hemoglobin, and blood lipid profile. In addition, stages and motivation for weight loss and the knowledge and perceptions in nutrigenomics and genetic testing will be evaluated.

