### Statistical analysis plan

2.10.

Outcome data will be reported following the Consolidated Standard Reporting Trials (CONSORT) guidelines (46). An intention-to-treat analysis will be employed.

The mean and standard deviation (SD) will be used to report continuous variables while percentages will be used for categorical variables. Estimates of the different sources of attrition bias will be conducted using two-way analysis of variance (ANOVA) models. Student *t*-test will be used to compare the differences in means between the intervention and the control group for the primary and secondary outcome measures. One-way ANOVA will be used if the comparison of multiple subclasses is warranted, with Dunn’s multiple comparisons *post-hoc* test. Linear mixed models will be used to determine changes from baseline among the different study outcomes, with participant number retained as random effect. A two-sided alpha of 0.05 will be used for hypothesis testing.

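### Weight is sized and motivated on a percent-loss scale, but the stated primary outcome and t-test compare mean weight between arms

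*Protocol article*

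**What the plan says.** Four places in the protocol article describe the weight question.

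- **Introduction (aim).** The trial is to determine whether the recommendation, given together with genetic-risk disclosure, "can help overweight/obese individuals achieve 5–10% weight loss in a 12-month trial when compared with the standard advice for weight management". BMI, waist and body fat follow as further primary outcomes.
- **2.5 Sample size calculation.** Fifty-two participants (26 per group) are "needed to detect a clinically meaningful difference of 5% weight loss after 6 months of intervention", with 80% power, 5% alpha and an SD given as 0.25 without a unit.
- **2.7 Outcomes.** "The primary outcomes will be the difference in weight, BMI, waist circumference, and body fat percentage between the arms after both the active and inactive" parts of the trial. The abstract words it in the same way. Neither mentions percent change.
- **2.10 Statistical analysis plan.** "Student *t*-test will be used to compare the differences in means between the intervention and the control group for the primary and secondary outcome measures". Separately, "Linear mixed models will be used to determine changes from baseline among the different study outcomes", with participant as random effect. No percent scale is given for that model and no arm term or arm contrast is stated.

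**The concern.** The quantity that motivates and sizes the trial is a percentage of each person's own starting weight. The quantity named for the primary test is weight. The two differ in variability. Overweight and obese adults with BMI from 25 to 40 kg/m² and differing heights vary widely in body weight, and that variation goes straight into the standard error of a t-test on attained weight. Percent change divides most of it out.

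Two things are at stake. First, a sample size built for one variable does not carry over to another, so a real effect of the size in 2.5 could easily be missed. Second, the result would come out in kilograms and could not be set directly against the 5% difference that the plan calls clinically meaningful, or against the 5–10% in the aim.

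**Working it through.** **1. The plan's own figure.** With the inputs of 2.5 read literally (difference 0.05, SD 0.25, two-sided 5%, power 80%):

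n per arm = 2 × (1.96 + 0.842)² × (0.25/0.05)² ≈ 393, not 26.

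Working back, 26 per arm corresponds to a standardised difference of about 0.78 (normal approximation) or 0.79 (t-test). For a 5-point difference that means an SD of about 6.3–6.4 percentage points. That the stated inputs do not give 26 is a separate matter. It is used here only to anchor a plausible SD on the percent scale.

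**2. Inputs for the comparison.**

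- From the protocol: 26 evaluable per arm, 1:1 allocation, two-sided alpha 0.05, 5% difference.
- Assumed, because the documents do not give them: mean weight 80 kg, so that 5% is 80 × 0.05 = 4 kg; between-person SD of attained weight 10–15 kg; SD of percent change 5–6.4 points.

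**3. Formula.** Power of the two-sample t-test with 50 df and non-centrality difference / (SD × √(2/26)), where √(2/26) = 0.2774. The smallest significant observed difference is 2.009 × SD × 0.2774.

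| Variable | Difference | SD (assumed) | Non-centrality | Power | Smallest significant difference |
|---|---|---|---|---|---|
| Attained weight | 4 kg | 10 kg | 1.44 | 29% | 5.6 kg |
| Attained weight | 4 kg | 12 kg | 1.20 | 22% | 6.7 kg |
| Attained weight | 4 kg | 15 kg | 0.96 | 16% | 8.4 kg |
| Percent change | 5 points | 5 points | 3.61 | 94% | 2.8 points |
| Percent change | 5 points | 6 points | 3.00 | 84% | 3.3 points |
| Percent change | 5 points | 6.4 points | 2.82 | 79% | 3.6 points |

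On attained weight, an observed difference of exactly 4 kg would not be significant at any of these SDs. By the normal approximation, 80% power would need 2 × (1.96 + 0.842)² × (SD/4)² evaluable per arm: 99 at SD 10 kg, 142 at 12 kg and 221 at 15 kg.

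**4. Where the gain comes from.** At 80 kg, an SD of 5–6.4 points is 4.0–5.1 kg of change. Change in kilograms would therefore have about the same power as percent change. What costs power is comparing attained weight instead of change. What favours percent over kilograms is agreement with 2.5 and the aim.

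**5. Does another stated analysis close the gap?** The mixed model addresses changes from baseline, so the plan does not ignore change. But the between-arm comparison of primary outcomes is assigned to the t-test, and the model is given neither a percent scale nor an arm contrast.

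**The case against.** **The protocol is condensed.** This is a journal article, and how weight is derived (kilograms, change or percent change) could be settled in the full protocol or a statistical analysis plan. That would answer a mere absence. Here, though, the article states the sizing quantity, the primary outcome and the test, and they do not agree. The phrase in 2.10 about comparing differences in means could also be taken as differences from baseline. That reading is possible, but 2.7 defines the outcome as a difference in weight between arms, and even then no percent scale appears.

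**Stratification.** Randomisation is stratified by BMI (2.8), which balances the arms on part of the variation. A plain t-test still counts that variation in its standard error.

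**A stronger reading.** A reader might infer that the aim is a responder question (more people reaching 5% on the intervention), that no stated analysis tests it, and that a positive trial would therefore not answer its own question. The text does not carry this. The aim names no proportion and reads equally well as a mean loss of that size. The abstract's introduction asks only whether weight loss is better, which a comparison of means can address. Calculations that set a t-test against a responder test mainly show that dichotomising loses power. With assumed true mean losses of 4% and 1% and SD 5, the shares reaching 5% are 42% and 21%, a real doubling. The t-test is significant in about 56% of simulated trials, and in about 31% it is significant while Fisher's test is not. Those 31% are misses by the weaker test and not false claims by the t-test.

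**Conclusion.** The point stands as a mismatch of scale: the trial is sized and motivated on percent weight loss, and its stated primary test is on mean weight. Under the assumptions above, the literal reading gives about 16–29% power for the 5% effect, against about 79–94% on the percent-change scale.

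These are illustrations and not the trial's actual power. They rest on an assumed mean weight of 80 kg and assumed SDs, and the low figures apply only if attained weight is compared without using baseline. It does not follow that a significant mean difference would be uninformative about the aim, nor that a responder test must decide the trial. The mismatch should be corrected before analysis, because choosing the scale after seeing the data would be open to challenge.

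**What to change.** In 2.7 and 2.10, define the primary weight variable as percent change in body weight from baseline. State that it is compared between arms with a 95% CI and reported alongside the 5% difference in 2.5.

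As a descriptive supportive result for the aim in the Introduction, report the proportion losing at least 5% of baseline weight in each arm, with the difference and its 95% CI. Do not make it a condition for the conclusion. In simulation with assumed mean losses of 4% v 1% (SD 5, 26 per arm), the observed proportion favoured the intervention in 99.7% of trials with a significant mean test. A condition on direction would therefore almost never bind, and a condition on significance would make the weaker test decisive.

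The cost is wording in two sections and one extra table. Weight is already measured at baseline and months 3, 6, 9 and 12. The one downside is that the responder comparison has less power than the comparison of means and should be presented as such.

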## Methods and analysis

2.

### Study design

2.1.

The MyGeneMyDiet^®^ study is a parallel-group, single-blind, randomized controlled trial (Figure 1). Sixty-two overweight or obese adults will be recruited through waves of study enrollment. The 12-month trial will entail an “active” phase (first 6 months), followed by an “inactive” phase from months 7–12. During months 1–6, all participants will receive three sessions of nutrition counseling, including general health and information presented in nutrition modules designed for the study. A simulation of a “free-living state” will be applied to the participants during months 7–12. During this period, a follow-up data collection on month 9 and the nutrition counseling session at the end of the study on month 12 will be initiated. The inactive phase will determine whether the participants continue to adhere to the dietary and lifestyle recommendations given to them during the active phase.

**Figure 1 fig1:**
[figure not shown]
The design of the MyGeneMyDiet^®^ Study.

### Recruitment and informed consent processes

2.2.

Invitation letters, social media promotions, and snowball sampling will be employed to recruit participants. Social media promotional materials will contain electronic links and contact information of the research team. Orientation sessions will be conducted via videoconferencing platforms such as Zoom webinars. Details of the study protocol and the informed consent form, including an open forum to tackle the rights and privileges of the participants, will be discussed during these sessions. The informed consent form will be emailed to the prospective study participants after the orientation.

### Eligibility criteria

2.3.

#### Inclusion criteria

2.3.1.

The trial targets overweight or obese individuals aged between 19 and 59, who indicate willingness to participate in the study. Their BMI should be equal to or greater than 25 but not more than 40 kg/m^2^. They should also have normal to pre-disease state level of fasting blood glucose, lipid profile, and blood pressure, and blood cortisol and thyroid hormone levels. They should carry at least one of the risk alleles of the three target genetic polymorphisms: A allele for *FTO* rs9939609, T allele for *TCF7L2* rs7903146, and G allele for *UCP1* rs1800592.

#### Exclusion criteria

2.3.2.

The exclusion criteria are as follows: individuals with elevated levels of fasting blood glucose, lipids, blood pressure, thyroid, and cortisol; self-reported history of heart disease; participation in a weight-loss program; adherence to a restrictive/therapeutic diet in the past 3 months; self-reported weight changes (greater than 3.0 kg); planned or recent bariatric surgery; consumption of weight altering medications and/or nutritional supplements that provide weight gain/loss in the past 6 months; clinical diagnosis of any mental disorder; current use of mental health medications; for females, pregnant, nursing, or with self-declared intention to become pregnant during the trial; and, current and anticipated enrollment in another research study.

The self-declared items in the exclusion criteria will be obtained using a questionnaire that will be provided during the registration to the trial. A licensed physician will be present during the screening visits to determine if a prospective participant is eligible to join the trial.

### Genetic counseling

2.4.

All participants, regardless of whether they will soon be randomized to either the intervention or control arm, will undergo pre-and post- genetic test counseling sessions. A genetic counselor will meet with the participants for a two-part, interactive, one-on-one virtual counseling. The pre-genetic test counseling will be scheduled a few days after the DNA sample collection and before genotyping of the samples. During this session, the genetic counselor will provide genetic education to the participants, with topics such as basic information about genes, chromosomes, genetic mutations, environmental and genetic interactions, and genetic testing procedures. The genetic counselor will also discuss the impact and potential emotional and psychological concerns that may arise from the result of the genetic test.

The post-genetic test counseling session will be conducted 2 weeks after the pre-test genetic counseling, in time for the release of the genetic testing results of the participants. The genetic counselor will disclose the genotyping results to the participants, along with psychosocial counseling to assist the participants in adapting the new information.

### Sample size calculation

2.5.

To address the primary research question, at least 52 participants (*n* = 26 per group) are needed to detect a clinically meaningful difference of 5% weight loss after 6 months of intervention, assuming 80% power, an alpha of 5%, and a 0.25 SD in the main outcome variable (31). We aim to recruit 62 participants (*n* = 31 per group) to account for the potential dropout rate of 20%.

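### The inputs printed in section 2.5 do not give 26 per group, and because the SD has no unit the power of the trial cannot be worked out from the article

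*Protocol article*

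**What the plan says.** Section 2.5 (Sample size calculation) of the protocol article sets a minimum of 52 participants, 26 per group, and gives its inputs as follows: "clinically meaningful difference of 5% weight loss after 6 months of intervention, assuming 80% power, an alpha of 5%, and a 0.25 SD". The statement carries a literature reference. No unit is attached to the 0.25, and the outcome scale (kilograms, percent change or proportion) is not named. The recruitment target is then raised to 62, 31 per group, for dropout.

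Section 2.10 (Statistical analysis plan) names a Student t-test for the comparison of the two arms on the primary and secondary outcomes, and adds: "A two-sided alpha of 0.05 will be used for hypothesis testing". Allocation is equal (section 2.8).

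**The concern.** The article prints everything a standard two-group calculation needs: difference, SD, alpha, power and the resulting number. A reader should be able to recover 26 per group from them and cannot. Since the SD has no unit, several readings are possible, and they give sample sizes from a handful to several hundred per group.

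This calculation is the only justification given for the size of the trial. If the inputs are wrong, nobody can say which difference between arms the trial can detect with 80% power. A non-significant result could then not be interpreted: it might be evidence against a 5-point advantage, or it might say almost nothing.

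**Working it through.** **Inputs**
- Difference between arms: 5% at 6 months (section 2.5).
- SD: 0.25, no unit (section 2.5).
- Power 80%, alpha 5% (section 2.5), two-sided (section 2.10).
- Test: two-sample t-test, 1:1 allocation (sections 2.10 and 2.8).
- Stated result: 26 per group (section 2.5).

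**Formula.** With d = difference / SD, the normal approximation is n per group = 2 × (1.960 + 0.842)² / d² = 15.7 / d². The exact t calculation adds about one per group. Exact figures are used below unless noted.

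**Attempt to reproduce 26 per group**

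| Reading of the printed inputs | d | n per group for 80% power | Power at 26 per group |
|---|---|---|---|
| 0.05 with SD 0.25 (or 5 points with SD 25 points) | 0.05 / 0.25 = 0.2 | 393.4, so 394 | 10.9% |
| 0.25 is itself the standardised difference | 0.25 | 252.1, so 253 | 14.3% |
| 0.25 is an ANOVA effect size f, used in a two-group t-test | 2 × 0.25 = 0.5 | 63.8, so 64 | 42% |
| 5 points with SD 0.25 points | 5 / 0.25 = 20 | a handful | about 100% |

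A one-sided test does not rescue the first row: it still needs 310 per group, and section 2.10 says two-sided in any case. Adjusting for baseline reduces n by the factor 1 − ρ². To bring 393 down to about 26, ρ would have to be about 0.97 (393 × (1 − 0.97²) is about 23; at ρ = 0.95 it is about 38). The article states no correlation.

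**What 26 per group does correspond to**
- At d = 0.8 the exact calculation gives 25.5, so 26 per group, with power 80.7%.
- The smallest d detectable with exactly 80% power at 26 per group is 0.79.
- If the difference is 5 points, the SD must be 5 / 0.79, about 6.3 points (6.25 if d is taken as 0.8).
- If the SD is 0.25, the detectable difference is 0.79 × 0.25, about 0.20, which is four times the stated 0.05.

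Neither an SD of about 6.3 points nor a difference of 0.20 appears in the article.

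**The case against.** The strongest objection is that the missing unit leaves open what calculation was run. An SD of 25 percentage points for six-month weight change is hard to credit, so a misprint or a lost unit is more likely than a design with 11% power. If the calculation used an SD of about 6.25 points, it was sound and only the text is wrong. This stands. A reader might infer from the first row of the table that the trial has 11% power and would almost always miss its planned difference. The article does not support that: it holds only if the SD is on the same scale as the 0.05, and another reading gives nearly 100%.

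A second objection is that some calculation with 0.25 can come close to 52 in total. If 0.25 was an ANOVA effect size f, a between-arm repeated-measures test over five visits needs 48 in total at a within-person correlation of 0.2 and 54 at 0.25. A two-visit arm-by-time test needs 54 and 50. Section 2.10 does mention linear mixed models. But this requires a correlation that is not stated and a different meaning for "a 0.25 SD in the main outcome variable". It limits the claim to the inputs as printed, under the stated t-test, and does not repair the text.

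A third is that the title calls the trial a pilot: "A study protocol for a pilot randomized controlled trial to evaluate the effectiveness". The label softens how a null result would be read. Section 2.5 nevertheless makes a formal power claim for the primary question, and section 2.10 plans hypothesis tests, so the claim should be right.

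Two further inferences should be resisted. One is that the 5% target is itself an error, because the Introduction reports that "Available evidence showed none or modest improvements in weight, lifestyle, and dietary behavior when advice was linked to genetic profiles". A trial may be sized for a clinically important difference without expecting it, and the Introduction frames its 5–10% aim as a comparison with standard advice. The other is a guess at how the slip arose, for instance that an SD was squared. A difference of 0.20 with SD 0.25 would give the same d of 0.8, and the article settles neither. The reference cited for the calculation was not available, so no SD can be judged realistic or unrealistic here. It could justify an SD, but it cannot make the printed figures yield 26.

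**Conclusion.** The point holds as an inconsistency. Under the two-sided two-sample t-test with 1:1 allocation, the printed difference, SD, alpha and power do not give 26 per group on any of the readings tabulated. The required number is 394, 253, 64 or a handful per group, depending on what 0.25 means, while 26 per group requires d of about 0.8.

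The actual power for the stated 5% difference is undetermined. At 26 per group it is about 11% if the SD is 0.25 on the scale where the difference is 0.05. It is about 14% if 0.25 is the standardised difference, about 81% if the SD is really 6.25 points, and close to 100% if the SD is 0.25 points. The article does not allow a choice between these, so the finding is that the justification is wrong as written, not that the trial is known to be underpowered.

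**What to change.** Correct section 2.5 as follows.

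1. Name the outcome and its scale, for example percent change in weight from baseline to month 6.
2. Give the SD on that scale, with its unit and source, and correct whichever input is misprinted.
3. State what 26 per group delivers: 80% power, two-sided 5%, for a between-arm difference of about 0.8 SD. That equals 5 points only if the SD is about 6.25 points.
4. If the SD really is 0.25 on the scale where the difference is 0.05, restate the power as about 11% and present the between-arm result as an estimate with a confidence interval.
5. If another method was used, such as a repeated-measures calculation, name it and give its correlation and effect-size definition.

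The cost is a change of wording. No extra participants are needed. The downside is that the corrected power or detectable difference may look less favourable than the present statement.

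### The recruitment target of 62 covers about 16% dropout, not the stated 20%: 62 × 0.8 leaves 49.6 against the 52 the plan says it needs

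*Protocol article*

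**What the plan says.** Section 2.5 (Sample size calculation) says that "at least 52 participants" are required, with "26 per group) are needed to detect a clinically meaningful difference of 5% weight loss after 6 months of intervention". The stated design values are "assuming 80% power, an alpha of 5%, and a 0.25 SD in the main outcome variable". The next sentence gives the enlarged target: "We aim to recruit 62 participants", 31 in each group, "to account for the potential dropout rate of 20" per cent.

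The same target appears elsewhere. The abstract (Methods and analysis) states: "Sixty-two overweight/obese individuals aged 19–59 years old will be recruited". Section 2.1 repeats sixty-two, and section 2.8 has 62 allocation envelopes prepared, 31 for each treatment. No section gives a larger target or says that dropouts will be replaced.

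**The concern.** Section 2.5 makes two linked statements: how many participants are needed, and how many must be recruited so that this number survives 20% dropout. Applying the stated rate to the stated target should return at least the stated minimum, and it does not.

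What is at stake is whether the dropout allowance does what the article claims. The 80% power is tied to 26 per group. If fewer remain at the plan's own dropout rate, the stated power does not hold at that rate, whatever the merits of the rest of the calculation. A reader of the trial report would also be told that 20% attrition had been planned for when the number recruited allows for less.

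**Working it through.** **Inputs**, from section 2.5 unless noted:
- Participants needed: 52 in total, 26 per group.
- Recruitment target: 62 in total, 31 per group.
- Dropout: 20%.
- Power 80% and alpha 5%; section 2.10 makes alpha two-sided.

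**Step 1. Reproduce the plan's figure.** Adding 20% to the required number gives 52 × (1 + 0.20) = 62.4 in total, or 26 × 1.2 = 31.2 per arm. Rounded down, these are 62 and 31, the figures printed. The article does not show its formula, so this is an inference, but the match is close.

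**Step 2. Apply the usual inflation.** If a share *d* is lost, the number to recruit is the number needed divided by (1 − *d*):
- In total: 52 / 0.80 = 65.
- Per arm: 26 / 0.80 = 32.5, rounded up to 33, so 66 with equal arms.

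These exceed the printed target by 3 and 4 participants.

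**Step 3. Check the printed target against the printed rate.**
- 62 × 0.80 = 49.6 remaining, against 52 needed: 2.4 short.
- 31 × 0.80 = 24.8 per arm, against 26 needed: 1.2 short.

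**Step 4. Find the dropout that 62 does cover.** 1 − 52/62 = 0.161, or about 16%. In whole participants, each arm can lose 31 − 26 = 5.

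**Step 5. Effect on power.** The article states no standardised difference, so one has to be assumed. Suppose that 26 per arm gives exactly 80% power with a two-sided t-test at 5%. The implied standardised difference is then about 0.79, and power falls with the number remaining as follows:

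| Remaining per arm | Power |
|---|---|
| 26 | 80.0% |
| 25 | 78.4% |
| 24.8 | 78.0% |
| 24 | 76.6% |

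At 20% dropout the loss is about 2 percentage points. Steps 1 to 4 take 52 as given and need no assumption about the effect size.

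**The case against.** **Timing.** Section 2.5 sizes the trial for a difference at 6 months, but the trial lasts 12 months and the article does not say when the 20% is reached. If 20% were the loss over the whole trial and attrition ran at a constant rate, loss by month 6 would be 1 − √0.8 = 10.6%. That would leave 62 × 0.894 = 55.5 participants, above 52. This stands as a condition on the finding. It does not remove it, because the natural reading of section 2.5 applies the 20% to the 52 being sized, and the whole-trial reading is nowhere stated. Under that reading the shortfall would fall at month 12, for which section 2.5 gives no required number.

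**Analysis.** Section 2.10 names an intention-to-treat analysis and linear mixed models, and weight is measured at months 3, 6, 9 and 12, so participants lost after month 3 could still contribute. This stands in part. The same section assigns the comparison of means between arms to a Student t-test, and a t-test of observed values at a visit uses only those measured then. Section 2.5 itself treats dropouts as lost; otherwise it would need no allowance.

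**Size.** The trial is described as a pilot, and the gap is 2 to 3 people. That is correct, and it limits the importance of the point. It does not make the sentence right, because section 2.5 justifies the number by a formal power statement.

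**Stronger readings that the article does not support.** A reader might infer that the trial is bound to have fewer than 52 participants at month 6. That does not follow while the timing of the dropout is unstated. A reader might also take a standardised difference of 0.8 as the plan's assumption and quote about 79% power for it. That value appears nowhere in the article and can only be worked back from 26 per group.

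**Conclusion.** The inconsistency is real and minor. At the stated 20% dropout, 62 leaves 49.6 participants (24.8 per arm), 2 to 3 fewer than the 52 that section 2.5 requires. The target covers about 16%. The likely cause is multiplying by 1.2 where division by 0.8 was needed.

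Two assumptions carry the conclusion. The shortfall at the sizing analysis assumes that the 20% is reached by month 6. The power of about 78% assumes that 26 per arm gives exactly 80% with a two-sided t-test; it is a reviewer's figure, not one from the plan. Whether 52 follows from the printed effect and SD is a separate question on which nothing here depends. A reader might infer that the trial is seriously underpowered because of this slip; a loss of about 2 percentage points does not support that.

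**What to change.** Amend the dropout sentence in section 2.5. Keep 62 (31 per group) and say three things:
- It allows for about 16% dropout.
- At 20% dropout about 25 per arm would remain, so power would be slightly below the stated 80%. If a figure is wanted, about 78% can be given, with the assumption that 26 per arm yields exactly 80% in a two-sided t-test.
- The month to which the dropout rate applies.

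If the sponsor wishes to keep both 52 and 20%, the matching target is 66 (33 per group). The abstract and sections 2.1 and 2.8, including the envelope count, would then have to change with it.

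A standardised difference of 0.8 should not be written in as the plan's effect size, because the article does not state one.

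Keeping 62 costs one or two sentences and a slightly less favourable statement of dropout or power. Moving to 66 costs four more participants.
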